## Abstract

**Introduction**: Falls are the leading cause of fatal and nonfatal injuries among older adults. Studies showed that older adults can reduce the risk of falls after participation in an unexpected perturbation-based balance training (PBBT), a relatively novel approach that challenged reactive balance control. This study aims to investigate the effect of the practice schedule (i.e., contextual interference) on reactive balance function and its transfer to proactive balance function (i.e., voluntary step execution test and Berg balance test). Our primary hypothesis is that improvements in reactive balance control following block PBBT will be not inferior to the improvements following random PBBT.

**Methods and Analysis**: This is a double-blind randomized controlled trial. Fifty community-dwelling older adults (over 70 years) will be recruited and randomly allocated to a random PBBT group (*n* = 25) or a block PBBT group (*n* = 25). The random PBBT group will receive eight training sessions over 4 weeks that include unexpected machine-induced perturbations of balance during hands-free treadmill walking. The block PBBT group will be trained by the same perturbation treadmill system, but only one direction will be trained in each training session, and the direction of the external perturbations will be announced. Both PBBT groups (random PBBT and block PBBT) will receive a similar perturbation intensity during training (which will be customized to participant’s abilities), the same training period, and the same concurrent cognitive tasks during training. The generalization and transfer of learning effects will be measured by assessing the reactive and proactive balance control during standing and walking before and after 1 month of PBBT, for example, step and multiple steps and fall thresholds, Berg balance test, and fear of falls. The dependent variable will be rank transformed prior to conducting the analysis of covariance (ANCOVA) to allow for nonparametric analysis.

**Discussion**: This research will explore which of the balance retraining paradigms is more effective to improve reactive balance and proactive balance control in older adults (random PBBT vs. block PBBT) over 1 month. The research will address key issues concerning balance retraining: older adults’ neuromotor capacities to optimize training responses and their applicability to real-life challenges.

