From a fall-prevention standpoint, an important aim of a PBBT is that learned motor skills (i.e., reactive balance performance) create a fast learning process, which can be generalized to a wide variety of everyday situations (i.e., real-life situations), which may require rapid balance recovery maneuvers. In general, motor learning research suggests that conditions during training should be varied randomly to optimize motor learning [challenge point framework (CPF; Guadagnoli and Lee, 2004)]. This would mean delivering perturbations from various directions in a randomized fashion during PBBT and different phases of the gait cycle. To our knowledge, no study has investigated whether a constant or random practice is more effective for motor skill acquisition, retention, and transferring motor tasks when older adults are training to improve their ability to recover from an unexpected loss of balance during walking. Our proposed study will incorporate similar principles with the use of a mechatronic device that can perturb participants unexpectedly and in multidirectional ways during treadmill walking. It is not known whether random PBBT better improves balance reactions in terms of the period of PBBT than block PBBT. In this research, we will address a key question about the generalizability of balance intervention and the underlying locomotor plasticity in older adults using random vs. block PBBT. The primary aim of this study is to determine the effect of block PBBT on reactive balance control among older adults (i.e., multiple- and fall-step thresholds). Our primary hypothesis is that improvements in reactive balance control following block PBBT will be not inferior to the improvements following random PBBT. The secondary purpose of this study is to determine the effect of block PBBT and random PBBT on balance proactive balance control and fear of falls. We hypothesize that, proactive balance, i.e., anticipatory balance control [Berg Balance Scale (BBS)] and fear of fall (FES-I), will cause similar effects in block PBBT and random PBBT.

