Sample sizes for each of the primary outcomes are outlined in Table 4. In regard to the fall threshold and the multiple-step threshold (backward), the sample size that was calculated for each group is similar, *n* = 19. A two-group one-sided 0.05 significance level *t*-test will have 80% power to reject the null hypothesis that the block PBBT and random PBBT are not noninferior [the difference in means of the fall threshold and multiple-step threshold (backward), μR − μB, is 2.00 and 1.90, respectively, or farther from zero in the same direction), in favor of the alternative hypothesis that the means of the two groups, i.e., block PBBT and random PBBT, are noninferior, assuming that the expected difference in means is 0.00 and the common standard deviation for the fall threshold is 2.40 and the common standard deviation is 2.00 for the multiple-step threshold (backward; based on an earlier study; Handelzalts et al., 2019). In regard to the multiple-step threshold (forward), the calculated sample size in each group is 8, and a two-group one-sided 0.05 significance level *t*-test will have 80% power to reject the null hypothesis that the block PBBT and random PBBT are not noninferior (the difference in means, μR − μB, is 1.90 or farther from zero in the same direction), in favor of the alternative hypothesis that the means of the two groups are noninferior, assuming that the expected difference in means is 0.00 and the common standard deviation is 1.40 (Table 2). To account for attrition rates reported to be about 25% involving training in older adults, (McMurdo et al., 2000) it was decided to include 25 participants in each group (19 × 1.25 = ~25) for a total of 50 participants.

**Table 4 T4:** Sample size estimation.

	Fall threshold	Multiple-step threshold (forward)	Multiple-step threshold (backward)
Test significance level α (one-sided)	0.05	0.05	0.05
Non-inferiority limit difference, Δ0	2.00	1.9	1.90
Expected difference, Δ1	0.00	0	0.00
Δ0 − Δ1	2.00	1.90	1.90
Common standard deviation, σ	2.40	1.4	2.0
Effect size, δ = |Δ0 − Δ1|/σ	0.833	1.357	0.826
Power, %	80	80	80
Sample size, per group, *n*	19	8	19

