### Statistical Analysis

Cohort descriptors and baseline values for primary and secondary outcomes will be compared between groups using Mann–Whitney *U* tests (continuous variables) or Fisher’s exact test (categorical variables). Measures that differ between groups at baseline may be used as covariates in the analysis of primary and secondary outcomes. To test the primary hypothesis, we will calculate the 95% CI for the post-intervention difference between groups (block PBBT minus random PBBT) for the primary outcomes [fall threshold and multiple-step threshold (backward and forward)]. Our hypothesis of non-inferiority will be supported if the lower limits of the 95% CIs are greater than the negative value of the non-inferiority limits (Schumi and Wittes, 2011). We will use both intention-to-treat and per-protocol analyses to test the primary hypothesis, as is recommended (Schumi and Wittes, 2011); per-protocol analysis will include only those participants who completed at least 80% of the training sessions. We will also use paired *t*-tests for each group individually to determine if the groups improve over time in the primary and secondary outcomes. To address the secondary objectives, we use analysis of covariance (ANCOVA) to compare the posttraining voluntary step execution test and postural sway parameters as well as the Berg Balance Score, Late-Life Function and Disability Index, and FES-I scores between groups, with the baseline value for each measure as a covariate. The dependent variable will be rank-transformed prior to conducting the ANCOVA to allow for nonparametric analysis.

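### The plan hypothesises similar effects on the Berg Balance Scale and FES-I, but its only between-arm analysis is a rank-based test for a difference, which cannot support similarity

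*Protocol article*

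**What the plan says.** The last paragraph of the Background sets out a secondary hypothesis for two outcomes, the BBS (as the measure of anticipatory balance) and the FES-I (fear of falling): they "will cause similar effects in block PBBT and random PBBT".

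Under Statistical Analysis, the between-arm method is: "To address the secondary objectives, we use analysis of covariance (ANCOVA) to compare the posttraining voluntary step execution test". The same sentence adds sway, BBS, the Late-Life instrument and FES-I, "with the baseline value for each measure as a covariate". The next sentence reads: "The dependent variable will be rank-transformed prior to conducting the ANCOVA to allow for nonparametric analysis". The Abstract repeats it: "The dependent variable will be rank transformed prior to conducting the analysis of covariance (ANCOVA) to allow for nonparametric analysis".

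For the primary outcomes, the same section uses a confidence interval and a margin: "Our hypothesis of non-inferiority will be supported if the lower limits of the 95% CIs are greater than the negative value" of the non-inferiority limits. No such limit, interval rule or other criterion is given for BBS or FES-I. The section also plans paired t-tests within each group, but these do not compare the arms.

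**The concern.** A hypothesis that two programmes act alike claims that any difference is too small to matter. The null of the planned ANCOVA is no difference at all. Not rejecting that null is what a small trial tends to produce whether or not the arms differ, so it is no evidence for the hypothesis.

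Ranking the outcome makes this harder to repair afterwards. The estimated group effect is a difference in mean ranks, which depends on the sample and has no BBS or FES-I unit. A reader cannot see from it how large a difference in points remains compatible with the data, and no clinical bound can be set on it directly.

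At stake is what the report can say about proactive balance and fear of falling. Improvement within both arms and no significant difference between them could easily be taken as similar effects while a sizeable difference is still possible.

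**Working it through.** **Inputs from the article.** 25 per arm are planned, 19 of them required as evaluable, with about 25% attrition (Power and Sample Size Calculation); allocation is equal (Recruitment, Randomization, Blinding, and Treatment Allocation).

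**Assumed, because the article gives no value for BBS or FES-I.** A benchmark difference of 0.5 SD; a baseline-outcome correlation r from 0 to 0.7; a two-sided 5% test; and, for equivalence, bounds of 0.5 and 0.8 SD.

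**1. The plan's own figure.** There is no sample size for the secondary outcomes. The primary figure for the fall threshold uses "A two-group one-sided 0.05 significance level" t-test, margin 2.00, SD 2.40 and 80% power. The effect size is 2.00/2.40 = 0.833. The noncentral t gives n = 19 per arm (power 80.9%), as stated. Applying 25% attrition to 25 gives 25 × 0.75 = 18.75, so 19 to 25 per arm is a fair range.

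**2. Chance of missing a 0.5 SD difference.** For ANCOVA with one covariate, λ = d / √[(2/n)(1 − r²)] with 2n − 3 degrees of freedom. Power comes from the noncentral t at the two-sided 5% critical value.

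| n per arm | r | λ at d = 0.5 | Power | Missed | Detectable with 80% power | Half-width of 95% CI |
|---|---|---|---|---|---|---|
| 19 | 0 | 0.5/0.324 = 1.54 | 32.3% | 67.7% | 0.94 SD | 0.66 SD |
| 19 | 0.7 | 0.5/0.232 = 2.16 | 55.5% | 44.5% | 0.67 SD | 0.47 SD |
| 25 | 0 | 0.5/0.283 = 1.77 | 41.0% | 59.0% | 0.81 SD | 0.57 SD |
| 25 | 0.7 | 0.5/0.202 = 2.48 | 67.9% | 32.1% | 0.58 SD | 0.41 SD |

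These rows are for ANCOVA on unranked, normal data. In a simulation of 3,000 trials (25 per arm, r = 0.7, normal data), ranking the outcome gave 63.5% power against 67.1% unranked. Ranking therefore moves the miss rate by only a few points, and it stays within the range above.

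**3. What a test aimed at similarity could show.** Two one-sided 5% tests (90% CI inside the bound), true difference zero, r from 0 to 0.7:

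| Bound | Power, 19 per arm | Power, 25 per arm | n per arm for 80% power |
|---|---|---|---|
| 0.5 SD | 2% to 36% | 10% to 57% | 69 down to 35 |
| 0.8 SD | 56% to 92% | 75% to 98% | 27 down to 14 |

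The last column uses n = 2(1 − r²)[(1.645 + 1.282)/bound]². For 0.5 SD and r = 0 this is 2 × (2.927/0.5)² = 68.5, so 69. Requiring a 95% CI inside the bound is stricter, so power would be lower. At r = 0 the expected half-widths (0.66 and 0.57 SD) already exceed a 0.5 SD bound.

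**4. Ranking the outcome but not the baseline.** Same simulation, 25 per arm, r = 0.7, shift of 0.5 SD on the underlying normal scale:

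| Data | Outcome only ranked | Both ranked |
|---|---|---|
| Normal | 63.5% | 63.4% |
| Ceiling at 56, BBS-like | 57.5% | 57.8% |
| Strongly skewed (lognormal) | 52.8% | 62.7% |

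With no true difference, rejection rates were between 4.5% and 5.1% for both versions in all three settings. The test stays valid, and power is lost only in the strongly skewed case.

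**The case against.** The strongest reply is that nothing in the article says p > 0.05 will be taken as proof of similarity. It says only that ANCOVA will compare the scores. The secondary purpose is worded as determining the effect of both programmes, and the Abstract asks which paradigm is more effective; a difference test fits both aims. The outcomes are secondary, the Limitations section describes the study as having a pilot character, and the primary conclusion has its own margin. A condensed article may also leave detail to a fuller plan.

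Part of this stands. A reader might infer a declared rule that non-significance equals similarity, but the article contains no such rule, and the misreading is a risk rather than a stated intention. The mismatch remains. The hypothesis as written is one of similarity, and the analysis attached to the secondary objectives cannot support it whatever the p-value. That is a method fixed in the text that does not fit its hypothesis, not a detail left out.

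Three stronger readings are also tempting and are not supported:

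- **All secondary outcomes are affected.** The similarity hypothesis names only BBS and FES-I. Stepping, sway and the Late-Life instrument share the ANCOVA but carry no such hypothesis.
- **Ranking only the outcome invalidates the adjustment.** The simulation shows otherwise. The text does not mention ranking the baseline, and that matters only for strongly skewed measures; nothing in the article says BBS or FES-I behave that way.
- **A 0.5 SD difference would be missed in 59% to 68% of trials.** Those figures give no credit for baseline adjustment, which the plan does specify. The fair range is 32% to 68%.

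**Conclusion.** The point holds for BBS and FES-I. The article hypothesises similar effects and fixes only a rank-transformed test for a difference. A non-significant result would not support the hypothesis, and the rank scale would not show what difference in points is excluded.

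The miss rate of about 32% to 68% depends on the assumed 0.5 SD benchmark and the assumed correlation. Whether 0.5 SD is clinically relevant on either scale cannot be judged from the article. The mismatch itself rests on none of these assumptions. It concerns secondary outcomes and leaves the primary non-inferiority comparison untouched.

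**What to change.** For BBS and FES-I, make the main between-arm result the baseline-adjusted difference (block minus random) on the original scale with its 95% CI, using a bootstrap interval if the scores are skewed. Then do one of the following:

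- State for each scale, before any between-arm results are seen, the bound within which the arms will be called similar, with its justification. Claim similarity only if the whole CI lies inside it.
- Reword the secondary hypothesis as exploratory estimation, with no claim of similarity.

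In either case, state that similarity will not be inferred from p > 0.05. Keep the rank ANCOVA as a sensitivity analysis, preferably with outcome and baseline both ranked; this last change is minor.

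No new data or participants are needed. The first option costs the work of choosing and defending a bound for each scale and, given the power figures above, will often give an inconclusive answer if the bound is near 0.5 SD. The second costs only rewording, but gives up the claim.

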### Adverse Events

Based on our previous studies, very mild adverse events related to PBBT have been reported, i.e., delayed-onset muscle soreness, fatigue, or exacerbation of joint pain in older adults (McMurdo et al., 2000; Kurz et al., 2016) and even in stroke patients (Handelzalts et al., 2019) with a similar frequency and severity of adverse events for both the PBBT and control groups, who completed more “traditional” balance training. Medical attention was not required for those who participated in the PBBT.

### Safety

Since the assessment and intervention are challenging for balance control, there is a small risk that older adults will lose his/her balance, especially during the balance recovery assessment. For that matter, we use a safety harness attached to a secure point overhead that will be worn for all postural perturbations to prevent a fall. Additionally, the research assistant or physiotherapist can provide assistance to prevent a fall. A similar harness system will be used during the interventions to ensure patient safety during the training session (see Table 2). In addition, training will be administered by a trained physiotherapy student that will tailor the training to the patient’s abilities. Assessments will be completed by a trained research assistant with a health sciences background. We have administered tens of thousands of postural perturbations with more than 100 older adults and about 40 stroke survivors with varying balance abilities in our previous research studies, and no one suffered an injury as a result of an induced balance perturbation. Also, in the cases where the participants were caught by the safety harness system or researcher, they did not suffer a physical injury. In case of a physical injury, the physiotherapist will provide first aid, will advise the participant regarding follow-up with medical aid, and will follow up with the participant after a day or so.

### Data Monitoring Committee

A data monitoring committee is not required for this study since the PBBT is a low-risk intervention for older adults. Adverse events that meet all three of the following criteria will be reported immediately to the institution’s research ethics board, as is routine practice: (1) unexpected in terms of nature, severity, or frequency; (2) related or possibly related to participation in the research; and (3) suggestion of a potential increase in risk of harm to research participants or others. All adverse events will be collated and evaluated biannually by the principal investigator.

### Trial Status

The study is currently recruiting participants. Enrollment began on February 1, 2019. We will complete the recruitment, training, and T1 and T2 data collection by March 1, 2021. We will complete the data analysis by December 31, 2021.

## Discussion

### Strengths

The perturbation training is not a novel intervention method, and the technology that provides unexpected perturbation during the treadmill walking method to improve balance function was used previously. The training methods presented here (random PBBT vs. block PBBT) are specific and incorporated progressive overloading and individualization. However, as far as we know, the comparison between random and block perturbation training methods to improve reactive balance was never examined in older adults. Our research project will investigate which training protocol will show generalization (positive transfer) or interference (negative transfer; random PBBT vs. block PBBT). Additionally, it will define if reactive balance control following block PBBT will not be inferior to the improvements following random PBBT.

This research will also address a key question about the generalizability of balance training and the underlying locomotor plasticity in older adults using gait perturbation as an innovative approach to improve balance reactive responses also in standing. The intervention will add physical activity to community-dwelling older adults. Therefore, our findings will be most likely improving their function and be directly relevant to active and healthy aging. We believe that the implantation of the best paradigm for training protocol into clinical interventions will reduce the incidence of falls in a highly efficient and cost-effective manner, especially for older adults. If we will find the benefits of random PBBT compared with block PBBT or vice versa, this would allow therapists and patients to more easily use a more customized fall-prevention training in their regular practice.

We are motivated by the work done recently by Takazono et al. (2020) which has explored the effects of the block and the random perturbation training on the stability of compensatory arm and leg movements (using the CALM scale; de Souza et al., 2019) in young participants. They found better generalization and retention performances in the random training group. Those results support our hypothesis and emphasize the need to explore those training schedules with older adults. The proposed amount of training in the block and random PBBTs is similar and exceeds that of previous studies of perturbation training in older adults.

### Limitations

There is a risk that both random PBBT and block PBBT methods introduced here might be difficult at the beginning of the training; thus, muscle soreness will occur. Also, there is a risk of balance loss and fall; however, we will use a harness system to ensure that a fall will not occur. Since PBBT is a challenging training approach, there is a risk that older adults will stop participating in the program (dropout). Because the outcome measures in this study are related to balance function and risk for falls, it is unlikely that our results will be definitive regarding the ability of these PBBTs to translate to a reduced number of falls and injurious falls among older adults. We will monitor real-life falls in a 1-year period post-intervention, using a diary and monthly telephone calls, but the sample size for such analysis will be too small. However, we assume that due to the low sample and relatively fit older adults, the improvement in balance function will not carry over to real-life falls. Our study will address relatively healthy independent older adults; therefore, the results could not be implemented on frail elderly or other populations. Also, since the number of participants is small, the study has a pilot character. Also, data analysis will address the following question: what is the optimal sample size for the primary outcome parameter, which will be used to estimate the sample size for the larger trial. Finally, although the assessor and the participants in this trial are blinded, the therapist delivering the intervention cannot be blinded to intervention allocation, which potentially introduces a source of bias.

## Ethics Statement

The studies involving human participants were reviewed and approved by Soroka Medical center approval #0396-16-SOR. The patients/participants provided their written informed consent to participate in this study.
